## Abstract

**Background:**

There is a need to find innovative approaches for translating best practices for chronic disease care into daily primary care practice routines. Primary care plays a crucial role in the prevention and management of cardiovascular disease. There is, however, a substantive care gap, and many challenges exist in implementing evidence-based care. The Improved Delivery of Cardiovascular Care (IDOCC) project is a pragmatic trial designed to improve the delivery of evidence-based care for the prevention and management of cardiovascular disease in primary care practices using practice outreach facilitation.

**Methods:**

The IDOCC project is a stepped-wedge cluster randomized control trial in which Practice Outreach Facilitators work with primary care practices to improve cardiovascular disease prevention and management for patients at highest risk. Primary care practices in a large health region in Eastern Ontario, Canada, were eligible to participate. The intervention consists of regular monthly meetings with the Practice Outreach Facilitator over a one- to two-year period. Starting with audit and feedback, consensus building, and goal setting, the practices are supported in changing practice behavior by incorporating chronic care model elements. These elements include (a) evidence-based decision support for providers, (b) delivery system redesign for practices, (c) enhanced self-management support tools provided to practices to help them engage patients, and (d) increased community resource linkages for practices to enhance referral of patients. The primary outcome is a composite score measured at the level of the patient to represent each practice's adherence to evidence-based guidelines for cardiovascular care. Qualitative analysis of the Practice Outreach Facilitators' written narratives of their ongoing practice interactions will be done. These textual analyses will add further insight into understanding critical factors impacting project implementation.

**Discussion:**

This pragmatic, stepped-wedge randomized controlled trial with both quantitative and process evaluations demonstrates innovative methods of implementing large-scale quality improvement and evidence-based approaches to care delivery. This is the first Canadian study to examine the impact of a large-scale multifaceted cardiovascular quality-improvement program in primary care. It is anticipated that through the evaluation of IDOCC, we will demonstrate an effective, practical, and sustainable means of improving the cardiovascular health of patients across Canada.

**Trial Registration:**

ClinicalTrials.gov: NCT00574808

## Background

The impact of cardiovascular disease (CVD) can be reduced by addressing key risk factors including smoking, obesity, and hypertension [1-3]. Primary care is central to the prevention and management of CVD. Ninety-five percent of Canadians with chronic disease have a regular family physician [4,5]. A majority of people perceive their primary care providers as a credible resource for health information and value their advice [6,7]. Primary care visits provide a unique opportunity to monitor patients' cardiovascular health and to initiate lifestyle changes and preventive care [8-10]. Unfortunately, most primary care practices are still transitioning from approaches that are designed to treat acute illnesses and are struggling to engage in high-quality management of chronic conditions such as CVD [11-13]. There exist significant care gaps, with recent studies showing that less than half of patients with diabetes have optimal blood glucose levels [14], and only 20% of patients with dyslipidemia are being actively treated [15]. In addition, despite the fact that smokers are two to four times more likely to develop coronary heart disease [16], a 2005 report released by the Canadian Tobacco Use Monitoring Survey indicated that only 54% of smokers who visited a healthcare provider in the study year received smoking cessation advice [17].

The Improved Delivery of Cardiovascular Care (IDOCC) through Outreach Facilitation project aims to improve the delivery of evidence-based care for the prevention and management of CVD in primary care practices through the use of practice outreach facilitation. The project is a multifaceted practice-tailored intervention that includes (a) audit and feedback and goal setting, (b) decision support for providers through the integration of an evidence-based cardiovascular care guideline, (c) practice delivery system redesign, (d) enhanced linkages to community resources for patients, and (e) patient self-management support tools. The intervention is delivered by a Practice Outreach Facilitator who helps incorporate these elements into daily practice routines, thus assisting physicians and staff in improving their delivery of evidence-based care for the prevention and management of cardiovascular conditions such as coronary heart disease, stroke/transient ischemic attack (TIA), peripheral vascular disease, renal failure, and diabetes. This innovative primary care quality-improvement trial is aligned with the chronic care model (Figure 1) and key findings from a recent systematic review by the Cochrane Effective Practice and Organization of Care (EPOC) Group on changing practice behavior [18]. In order to initiate positive, sustainable changes in practice behavior to improve chronic disease care, interventions should (a) be multifaceted [19], (b) be practice-tailored [20], and (c) involve system-level changes based on the elements of the chronic care model (Figure 1) [21].

**Figure 1 F1:**
[figure not shown]
**The chronic care model, as described by Wagner et al, **[13]**identifies six essential elements for appropriate care of people with chronic diseases: **1) community linkages, 2) health care organization, 3) delivery system redesign, 4) clinical information systems, 5) decision support, and 6) self-management support for patients. Taken collectively, these six elements are intended to produce effective interactions between proactive prepared practice teams and informed activated patients who take an active part in their care. (Image from http://www.improvingchroniccare.org).

Several other facilitation studies have looked at cardiovascular care [22-26], but none of these investigations have examined the impact of facilitation and its sustainability at the same depth and breadth as has the IDOCC project. Although proven to be efficacious in improving preventive care delivery in other areas of medicine, the generalizability of facilitation in a Canadian healthcare setting still remains unclear, as all investigations conducted to date have taken place in highly controlled small-scale settings, with the interventions being focused on a select group of primary care models in either urban or rural areas [27-31]. IDOCC is the first Canadian study, and one of the first studies worldwide, to examine the effectiveness of facilitation on cardiovascular care in a real life setting using a pragmatic design.

The primary research question in IDOCC is as follows: Does the large-scale implementation of a quality-improvement intervention in cardiovascular care impact (a) practice adherence to evidence-based cardiovascular care guidelines and (b) patient clinical outcomes.

This article outlines the research methods used in the IDOCC project. Unique features include the use of the stepped-wedge design, mixed methods, and the incorporation of the chronic care model approach. We hope to demonstrate that the use of practice outreach facilitation, grounded in the chronic care approach, can be successfully translated into different Canadian primary care organizations as an effective, practical, and sustainable means of improving cardiovascular health.

## Methods/design

### Overview

IDOCC is a stepped-wedge cluster randomized control trial where Practice Outreach Facilitators work with primary care practices to optimize CVD prevention and management in those patients at high risk. The multifaceted intervention, based on the chronic care model, is being offered over a 24-month period. The primary outcome is a composite score measured at the level of the patient to represent each practice's adherence to evidence-based guidelines for CVD care.

### Design

This cluster randomized control trial employs a stepped-wedge design. A stepped-wedge design is a type of crossover study in which clusters cross over from the control arm to the intervention arm at different time points [32]. The IDOCC program is being offered to practices randomly assigned by region to one of three distinct steps (26-30 practices per step), with each consecutive step (or cohort of practices) beginning the program approximately one year apart. The intervention is delivered to practices over a two-year period (Figure 2):

**Figure 2 F2:**
[figure not shown]
**IDOCC Step-wedge study design**.

1. Year 1 - Intensive Phase: Practices receive Outreach Facilitator visits every three to four weeks.

2. Year 2 - Sustainability Phase: Project intensity is lessened, with Facilitator visits every 6 to 12 weeks.

At the end of Year 2, a follow-up patient medical chart audit is used to examine changes in adherence to guidelines and patient clinical outcomes between baseline and Year 1 and baseline and Year 2 of the intervention (see section on Project Outcomes). The time offset in the rollout of the intervention allows us to control for secular changes over time as subsequent steps act as a control for previous steps. For example, when examining the impact of the intensive phase of the intervention, Step II practices will serve as controls for Step I practices, and Step III practices will serve as controls for Step II practices (Figure 2). Specific comparisons of interest in this project along with their temporal controls are presented in Table 1. Table 2 presents the progress of the IDOCC project.

**Table 1 T1:** IDOCC study comparisons

Phase	Step	Change in outcome	Temporal/societal control
Intensive	I	X_SI, T2 _- X_SI, T1_	X_SII, T2 _- X_SII, T1_
	
	II	X_SII, T3 _- X_SII, T2_	X_SIII, T3 _- X_SIII, T2_

Sustainability	I	X_SI, T3 _- X_SI, T2_	X_SIII, T3 _- X_SIII, T2_
	
	II	X_SII, T4 _- X_SII, T3_	----

Overall study	I	X_SI, T3 _- X_SI, T1_	X_SIII, T3 _- X_SIII, T1_

SI = Step I, SII = Step II, SIII = Step III, T1 = Time Period 1, T2 = Time Period 2, T3 = Time Period 3, X = a quality-of-care outcome or a patient clinical outcome.

Note: There is no control for the Step II sustainability phase

**Table 2 T2:** Study design and progress of IDOCC program participation of practices and physicians as of April 2011

	IDOCC program		
		
Study Design	Intensive phase	Sustainability phase	Final data collection

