### Sample-size calculation

Prior to the recruitment phase of this project, a series of simulations were run on patient data from a pilot phase of the chart audit in order to examine how the primary outcome composite score varied with specific changes in physician adherence to recommended guidelines. For example, if Patient X had diabetes and a composite score of Y, how would Patient X's composite score change if he/she now had (a) a discussion about glycemic control medications with his/her physician? (b) a lipid profile test performed? (c) both maneuvers performed? The results from each simulation were discussed amongst a panel of family physicians and cardiologists in order to assess what effect size or change in composite score would represent a clinically relevant change in provider performance. From these discussions, it was agreed that an effect size (mean difference in the composite score for practices in the intervention step vs. the comparison step) of 8% represented a clinically relevant change. Using the sample-size calculation formulas for comparing two means presented by Donner and Klar [45], and assuming an intra-cluster correlation coefficient (ICC) of 0.18, a common standard deviation of 18%, and an average of 66 charts per practice, we would require 21 practices per step to detect an 8% difference using a two-sided test at the 5% level of significance with 90% power. To account for 20% potential attrition, a total of 27 practices per step were enrolled. The ICC and standard deviation used for this calculation were derived from the IDOCC pilot project on nearly 500 patients across seven practices. The anticipated attrition rate accounted for both practice-level as well as patient-level attrition and was based on experience from previous practice-based research studies [27-29].

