### Quantitative analysis

Descriptive statistics will be generated for all project variables (means and standard deviations for continuous variables with normal distributions or medians and interquartile ranges for skewed distributions, and frequencies and proportions for categorical variables). These statistics will be compared among the practices allocated to the different steps of the stepped-wedge design to assess imbalances in practice characteristics that would need to be controlled for in the analyses, including age, sex, practice model type, urban/rural practice setting, practice size, patient socioeconomic status (determined using a census-based method [46]), and patient comorbidities. Physicians agreeing to participate in the project will be compared to those declining to participate, and those characteristics significantly associated with participation will be adjusted for in secondary analyses to explore the potential impact of participation bias on our results. All analyses will be conducted using a commercially available software package (SAS, Version 9.2, SAS Institute, Inc., Cary, NC, USA [47]) with α = 0.05 as the level of significance.

Although the practice is the unit of intervention, all process and clinical measurements are at the patient level, and as such, the patient is the unit of analysis. All primary and secondary outcomes will be analyzed using general linear mixed-effects regression models using the stepped-wedge design analysis approach outlined by Hussey and Hughes [48]. All models include random effects for practice to account for the ICC of patients within the same practice, as well as fixed effects for region (the stratification used in the randomization scheme).

Prespecified controlled comparisons (Table 1) among practices in specific steps will be made in the regression models to examine the impact of the intervention while controlling for the effects of time. For example, in order to estimate the impact of the intensive phase of the project on Step I practices, a comparison of the patients in the intervention (Step I) and control (Step II) groups will be done by comparing the mean changes in the primary (*i.e*., QOC composite score) and secondary outcomes from baseline (Time Period 1) to the intensive phase year (Time Period 2) (Table 1).

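### The Step I intensive-phase effect is compared with Step II alone although Step III is also unexposed, and the two step-specific intensive rows are not reconciled with the joint model

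*Protocol article*

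**What the plan says.** The Design section and Table 1 of the protocol article set out five comparisons.

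- **Intensive phase, Step I:** change from T1 to T2, with Step II as the only control. The text says "when examining the impact of the intensive phase of the intervention, Step II practices will serve as controls for Step I practices".
- **Intensive phase, Step II:** change from T2 to T3, with Step III as control.
- **Sustainability, Step I:** change from T2 to T3, with Step III as control.
- **Sustainability, Step II:** change from T3 to T4. The table adds: "Note: There is no control for the Step II sustainability phase".
- **Overall study, Step I:** change from T1 to T3, with "X_SIII, T3 _- X_SIII, T1" as control.

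Step III is therefore used at T1 in the overall row and at T2 in two other rows. No row combines the two intensive-phase estimates.

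The Quantitative analysis section analyses all outcomes in mixed models following Hussey and Hughes. It says that the controlled Table 1 comparisons are prespecified and made within those models, and it repeats Step I against Step II as its worked example. It runs all analyses "with α = 0.05 as the level of significance". The Sample-size calculation refers to one unspecified pair of steps: "mean difference in the composite score for practices in the intervention step vs. the comparison step) of 8% represented a clinically relevant change".

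**The concern.** In a stepped-wedge trial every cluster that has not yet crossed over informs the period effect. Over T1 to T2 both Step II and Step III are waiting, and the Step III data for those periods are to be collected anyway. Naming Step II alone gives up precision at no saving.

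The plan also points two ways. A Hussey and Hughes model fits all steps and periods together with a common treatment effect. Table 1 asks for step-specific differences between pairs of steps. The article does not say whether Step III informs the Step I estimate, or whether a common intensive-phase effect will be reported at all. At stake are the precision of the main result and what the trial reports if the Step I and Step II rows differ.

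**Working it through.** **1. The plan's own sample size.** Inputs from the Sample-size calculation: difference 8%, "intra-cluster correlation coefficient (ICC) of 0.18, a common standard deviation of 18%, and an average of 66 charts per practice", and a design "to detect an 8% difference using a two-sided test at the 5% level of significance with 90% power".

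- Design effect: 1 + 65 × 0.18 = 12.7.
- Patients per group without clustering: 2 × (1.960 + 1.282)² × 0.18² / 0.08² = 106.4.
- Practices per step: 106.4 × 12.7 / 66 = 20.47, rounded up to 21. With 20% attrition, 21 / 0.8 = 26.25, rounded up to 27.

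Both stated figures reproduce. The trial is sized for one two-step comparison at the full 5%.

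**2. Wider control for Step I.** Table 2 gives 26, 30 and 27 practices in Steps I, II and III. Assume equal charts per practice, exchangeable errors between periods, no attrition and no region-level variance. The variance of a difference in changes is then proportional to 2(1/K₁ + 1/K₀), where K₁ and K₀ are the numbers of intervention and control practices.

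- Step II as control: 2(1/26 + 1/30) = 0.1436.
- Steps II and III as control: 2(1/26 + 1/57) = 0.1120.
- SE ratio: √(0.1120 / 0.1436) = 0.883, a cut of 12%. The variance is 22% lower.

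Counting regions, the randomised units, 3 against 6 instead of 3 against 3 gives √[(1/3 + 1/6) / (1/3 + 1/3)] = 0.866, a cut of 13%.

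**3. Pooled intensive-phase effect.** Weighted least squares on step-by-period means over T1 to T3, with step and period effects and separate intensive and sustainability effects, gives a variance factor of 0.0543.

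| Estimate | Variance factor | SE relative to Step I vs II row |
|---|---|---|
| Step I vs II (Table 1) | 0.1436 | 1 |
| Step II vs III (Table 1) | 2(1/30 + 1/27) = 0.1407 | 0.99 |
| Simple average of these two rows | (0.1436 + 0.1407 + 2/30) / 4 = 0.0877 | 0.78 |
| Pooled, all steps, T1 to T3 | 0.0543 | 0.62 |

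The 2/30 term arises because the two rows share the Step II mean at T2. The pooled SE is 38% below the single row, and √(0.0543 / 0.0877) = 0.787 puts it 21% below the simple average.

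**4. Dependence on Step III at T3.** If Step III at T3 cannot count as unexposed and is dropped, the T3 period effect and the sustainability effect absorb the remaining T3 means. The pooled estimate then reduces to the contrast in step 2, with factor 0.1120 and a 12% gain.

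**5. Absolute scale.** The per-period variance of a practice mean, net of its stable part, is SD² × ICC × (1 − c) + SD² × (1 − ICC)(1 − r) / 66, where c is the cluster autocorrelation and r the within-patient correlation. The article gives neither. At c = 0.8 and r = 0.5 (assumed) this is 0.00137, so the SEs are 1.40 points (Step I vs II), 1.24 (wider control) and 0.86 (pooled). For c from 1 to 0.5 and r of 0 or 0.5, the SE of the Step I vs II row runs from 0.54 to 2.18 points, and its power for 8 points is at least 95.6%.

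**6. Several rows at 5%.** Simulating the four controlled rows under the null with their shared means (2,000,000 draws), at least one two-sided rejection occurs in 16.7%, and at least one false finding of benefit in 8.6%.

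**The case against.** The strongest reply is that the named model may already do what is asked. A Hussey and Hughes model uses every step and period, and the Table 1 comparisons are made inside it. This stands in part. A reader might infer that the trial throws Step III data away, but the article does not show that: other rows use those data, and the model may bring them into the Step I estimate. What remains is that Table 1 and the worked example both name Step II as the only control, and nothing reconciles them with a joint model.

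A reader might also take the 38% as the cost of omitting Step III. It is not. It compares a pooled estimate with a single row, and averaging the two existing rows already gains 22%. The like-for-like cost is 12%. Nor is the trial underpowered for its 8-point difference: at an SE of 1.40 that difference is 5.7 standard errors.

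A third inference is a type I error near 17%. The article nowhere says that success follows from any one significant row. The rows ask different questions, and about half of those rejections would be in the direction of harm. A primary contrast and a multiplicity rule may also sit in an analysis plan that is not shown.

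Finally, Step III might be called the cleaner control because Step II starts in April 2009 while Step I's intensive phase ends in January 2010. The same Table 2 has Step III starting in January 2010 while Step II's intensive phase runs to March 2011. Calendar overlap therefore affects both controls, and it bears on any estimate that uses Step III at T3, including the existing Step II row.

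**Conclusion.** The point holds as a loss of precision that costs nothing to avoid, together with an unclear link between Table 1 and the model. If the Step I intensive contrast is run as Table 1 states it, its SE is about 13% larger than it need be (1 / 0.883 = 1.13); equivalently, adding Step III cuts it by about 12%. A pooled intensive-phase effect would improve on the single row by about 38% and on the average of the two rows by about 21%.

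These ratios assume exchangeable errors, equal charts per practice, the enrolled 26, 30 and 27 practices, and no region-level variance, although regions were randomised. The pooled gain further assumes similar intensive effects in Steps I and II and an unexposed Step III at T3; without the latter it falls to 12%. The chance of a false positive across the four controlled rows, about 17% two-sided or about 9% for false benefit if all were read as equal tests, is a supporting point and not the main harm.

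**What to change.** - In Table 1 and the worked example, use Steps II and III together as the control for the Step I intensive contrast.
- State that the main intensive-phase estimate for the QOC score is the pooled effect over Steps I and II from the single Hussey and Hughes model with period effects, using all unexposed practice-periods, and with the sustainability phase as a separate effect.
- Keep the step-specific, sustainability and overall contrasts as secondary, and report the uncontrolled Step II sustainability row descriptively.
- Define the calendar boundaries of T1 to T4 and check them against the Table 2 start dates, above all for Step III at T3. If exposed Step III time falls within T3, say how it is handled.

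The cost is analysis wording only, with no new data. The price of pooling is the assumption of a similar intensive effect in Steps I and II; the step-specific estimates, kept as secondary results, let readers judge it.

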**Step I - First cohort of practices** **(26 practices, 59 physicians)**			

Start:	April 2008	April 2009	July 2010

Completed as of April 2011:	26 practices, 59 physicians	26 practices, 59 physicians	26 practices, 59 physicians

Projected completion:	January 2010 (Complete)	January 2011 (Complete)	February 2011 (Complete)

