**Step II - Second cohort of practices** **(30 practices, 79 physicians)**			

Start:	April 2009	April 2010	October 2011

Completed as of April 2011:	30 practices, 79 physicians	1 practice, 2 physicians	--

Projected completion:	March 2011 (Complete)	March 2012	September 2012

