**Step III - Third cohort of practices** **(27 practices, 53 physicians)**			

Start:	January 2010	January 2011	July 2012

Completed as of April 2011:	13 practices, 25 physicians	--	--

Projected completion:	June 2011	June 2012	June 2013

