### Practice recruitment

Prior to the initiation of the recruitment process for each step, we developed an up-to-date list of the contact information of all physicians practicing in the geographic regions of interest using a variety of physician listings, such as The College of Physicians and Surgeons of Ontario website, the yellow pages, the provincial directory of group practices and through direct contact with the practices. Practice recruitment was carried out using a modified Dillman approach involving reminders and repeat mailings [35]. While no compensation was offered to practices for participation, a pre/post-intervention chart audit measuring the quality of their practice's overall cardiovascular care and the opportunity to obtain continuing professional development credits upon completion of the program (15 Mainpro-C credits, http://www.cfpc.ca/MainproCCredits/ acted as incentives. Practices were enlisted into the IDOCC program if at least one physician from that practice agreed to participate in the project. Practices agreeing to take part in the project were asked to fill out a practice-characteristic survey highlighting details about their practice, including number of patients for the physician, primary care model type, years in practice, etc. The consent signed by each physician allowed the project team to collect information from their patient medical charts and to link this information to the province's health administrative databases. Practices entered the project immediately after consenting to the project. We also completed nonparticipant surveys for the practices that decided not to take part in the project. The purpose of the survey is to identify reasons for not wanting to participate and collect data on practice characteristics so that we could assess participant selection bias.

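### On the Table 2 dates, the contrasts that use Step III at T3 cannot have controls that are both concurrent and unexposed

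*Protocol article*

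**What the plan says.** The Design section describes three steps, "with each consecutive step (or cohort of practices) beginning the program approximately one year apart". Each practice then has two one-year phases, the first being "Year 1 - Intensive Phase: Practices receive Outreach Facilitator visits every three to four weeks". For the intensive phase, "Step II practices will serve as controls for Step I practices, and Step III practices will serve as controls for Step II practices".

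Table 1 puts treated and control steps on the same numbered periods. Step III is the control at T3 for Step II intensive and Step I sustainability, both with "X_SIII, T3 _- X_SIII, T2", and for Step I overall, with its change from T1 to T3. The text gives T1 to T4 no calendar dates. The Quantitative analysis section says these prespecified contrasts control for the effects of time.

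Table 2 gives the dates reached or projected as of April 2011. The Practice recruitment section adds that "Practices entered the project immediately after consenting to the project". The Post-intervention section says that control data, labelled Baseline-C, come from before the intervention and are abstracted once Year 2 has ended in each practice.

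**The concern.** A shared period label removes secular change only if the treated and control windows cover the same calendar time and the control window is free of intervention. Table 1 assumes both. The Table 2 dates do not allow both for Step III at T3, because Step III began nine rather than twelve months after Step II and practices within a step began at different times.

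Two readings remain, and the text does not settle which applies:

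- **Periods are calendar years.** Some Step III control months are intervention months, and a real benefit is understated.
- **Control years are each practice's own pre-intervention years.** The controls are clean but describe an earlier time, so the contrast does not fully control for time unless the trend is roughly linear.

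The primary composite score is analysed through these contrasts. T3 cannot simply be cut to nine months, since most Table 3 indicators look back over a year.

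**Working it through.** **Inputs (Table 2; months counted from April 2008 = 0)**

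| Step | First intensive start | Intensive completion | Span |
|---|---|---|---|
| I | April 2008 (0) | January 2010 (21) | 21 |
| II | April 2009 (12) | March 2011 (35) | 35 − 12 = 23 |
| III | January 2010 (21) | June 2011, projected (38) | 38 − 21 = 17 |

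Step I sustainability runs from April 2009 (12) to January 2011 (33). Spans of 17 to 23 months for a one-year phase fit rolling entry.

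**The plan's own figure.** Patients per arm: 2 × (0.18 × (1.960 + 1.282) / 0.08)² = 106.4. Design effect: 1 + 65 × 0.18 = 12.7. Practices: 106.4 × 12.7 / 66 = 20.5, so 21 per step. With 20% attrition: 21 / 0.8 = 26.25, so 27. The sample size reproduces and is not in dispute; it is used only for the illustration below.

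**Step 1: first-start dates alone.** Overlap = end of the earliest treated year − first control start.

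- Step I intensive vs Step II: 0 + 12 − 12 = 0 months.
- Step II intensive vs Step III: 12 + 12 − 21 = 3 months.
- Step I sustainability and overall vs Step III: 0 + 24 − 21 = 3 months.

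**Step 2: completion counts, without assuming how entry was spread.** By April 2011 all 30 Step II practices had finished the intensive phase but only 1 had finished sustainability. With 12-month phases, 29 of 30 therefore started after about April 2009, and their intensive years ended after about April 2010. In Step III, "13 practices, 25 physicians" of 27 practices and 53 physicians had finished the intensive phase, so those practices started by about April 2010. At least 29/30 × 13/27 = 47% of Step II/III pairs overlap to some extent.

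**Step 3: average under uniform entry and exact 12-month phases (assumptions).** Last start = completion − 12. Starts run 0–9 in Step I (mean 4.5), 12–23 in Step II (mean 17.5) and 21–26 in Step III (mean 23.5). Offset = end of treated year − control start; overlap is the offset truncated to 0–12. The last three columns are from one million simulated pairs.

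| Contrast | Mean offset | Mean overlap | Pairs overlapping | Maximum overlap |
|---|---|---|---|---|
| Step II intensive vs III | 17.5 + 12 − 23.5 = 6.0 | 6.0 months | 96% | 12 |
| Step I sustainability vs III | 4.5 + 24 − 23.5 = 5.0 | 5.0 months | 96% | 12 |
| Step I intensive vs II | 4.5 + 12 − 17.5 = −1.0 | 1.2 months | 41% | 9 |

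Step I overall uses the same T3 years as Step I sustainability.

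**Step 4: consequence if periods follow the calendar.** If the full effect were immediate and diluted in proportion to exposed months, 8 points would become 8 × 9/12 = 6 (3 months) or 8 × 6/12 = 4 (6 months). With 21 practices per step, SE = 0.18 × √(12.7/66 × 2/21) = 0.0244, and power falls from 90.7% to 69% or 38%. If the effect takes longer to appear than the overlap lasts, there is little or no dilution. The range is thus 6 to 8 points at 3 months and 4 to 8 at 6 months.

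**Step 5: consequence if control years are pre-intervention.** The offset becomes a calendar shift h. Control years end on average 6 months before the intervention years for Step II vs III (from 2 months later to 14 months earlier), and 5 months before for Step I sustainability vs III (from 2 later to 12 earlier). For Step I intensive vs II the mean absolute shift is 3.5 months. Under a linear trend, a one-year change is the same wherever the window sits, so the bias is zero. If the yearly secular change itself grows by g points per year, the bias in a one-year contrast is g × h/12: g/2 at 6 months and 5g/12 at 5 months. Its sign is that of g, and the documents give no value for g.

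**The case against.** The strongest counter-argument is that overlapping rollout dates are not overlapping measurement windows. A reader might infer from Table 2 that the next step was already treated throughout its control year, that every Table 1 contrast is contaminated, and that half of an 8-point effect is lost. The documents do not support that. The Post-intervention section describes control data as preceding the intervention, which points to misalignment in time rather than exposure. Table 1 also compares changes, not levels, so a shifted window biases the result only if the trend bends. Steps I and II start exactly 12 months apart, so the worked example in Quantitative analysis is nearly intact. The averages rest on uniform entry and exact 12-month phases, and proportional dilution is close to a worst case, because a practice's first months go to audit feedback, consensus building and goal setting.

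All of this stands, and it limits the size of the problem. It does not remove it: no common set of 12-month periods keeps Step III as a whole unexposed through Step II's intensive year.

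It can also be said that Figure 2, which is not shown, or a fuller plan may date the periods. That is possible, but dating them only decides which of the two problems applies.

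**Conclusion.** The concern holds for the three contrasts that use Step III at T3. On the stated dates, their controls are either partly exposed or not concurrent. The 3-month gap follows from first-start dates and a one-year phase. The 5 to 6 month averages also need uniform entry. Calendar-aligned periods would bias a beneficial effect toward zero. Pre-intervention control years, the reading the text favours, leave a bias of unknown size and direction that vanishes under a roughly linear trend. Contamination is not demonstrated, and Step I intensive versus Step II is only slightly affected.

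**What to change.** In the mixed model, replace the T1–T4 labels with each practice's actual start date and dated 12-month windows. Use fixed effects for calendar time, set the exposure phase by months since that practice's own start, and count a window as control only if it ends before that start. This fits the stepped-wedge mixed model already planned.

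Apply the dated windows in the audits that, as of April 2011, were still to come: Step II (from October 2011) and Step III (from July 2012). Step I's audit was complete by February 2011, so new abstraction instructions cannot reach it; use the dates already recorded there. Reconcile the statement on one-year spacing and Table 1 with Table 2, and say which reading of T3 was intended.

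The work is wording in the analysis plan and abstraction manual. The statistical cost is less concurrent control information for Step II, above all for late-starting practices, and so wider intervals for the Step III-controlled contrasts.
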